#### Secondary Endpoints

The secondary endpoints are:

Changes in symptoms of depression from baseline to week 8 as measured by the Clinical Global Impressions (CGI), Snaith-Hamilton pleasure scale (SHAPS), and Quick Inventory of Depressive Symptomatology (QIDS)-SR16 scores.Changes in symptoms of anxiety from baseline to week 8 as measured by the generalized anxiety disorder (GAD)-7 and Hamilton anxiety rating scale (HAM-A) scores.Changes in immune marker concentrations from screening to week 4 and week 8.Changes in symptoms of depression and anxiety from baseline to week 2, week 4, week 6, and the 2-week follow-up measured using the MADRS, HAM-A, and GAD-7 scores.Changes in relative abundance, diversity, and level of engraftment in stool samples, as measured by 16S rRNA sequencing.

### Assessments of Safety and Efficacy

#### Primary Clinical Measures

Mood will primarily be assessed using the MADRS, a 10-item clinician-rated questionnaire used to evaluate the severity of depression.

#### Secondary Clinical Measures

Anxiety will primarily be assessed using the HAM-A, a clinician-rated questionnaire that measures the severity of anxiety symptoms. The GAD-7, a 7-item questionnaire, will be used to measure self-reported anxiety symptoms and severity. The CGI scale is a 2-item clinician-rated scale that will be used to assess the severity of illness and improvement of symptomology over time. The SHAPS is a 14-item self-rated instrument used to assess the presence of anhedonia. The QIDS-SR16 is a 16-item questionnaire that measures self-reported depressive symptom severity. The Pittsburgh Sleep Quality Index is a 19-item self-report questionnaire used to assess sleep quality and disturbances. Early life stress will be assessed using the Childhood Experience of Care and Abuse questionnaire to determine the effects of maltreatment and upbringing on treatment response and MDD biomarkers.

Participants will also use a personal log to track any newly emerging GI symptoms since the beginning of treatment to assess their tolerability to treatment and keep track of their mood symptoms and sleep. Tolerability and GI effects will be assessed using the Toronto Side Effects Scale and the GI Symptom Rating Scale during all treatment-related visits.

#### Molecular Analysis

Stool samples will be collected and analyzed using 16S ribosomal RNA sequencing at the University of Guelph. These data will be used to assess the relative abundance of microbial species, level of engraftment of MET-2 species, and α and β diversity of the gut microbiome. Urine samples will be collected to analyze soluble metabolites at the University of Guelph, whereas blood samples will be collected for clinical chemistry, hematology, and additional biomarker testing for safety and discovery purposes at Life Labs and Queen’s University, respectively. Statistical analyses will be performed to assess the relationship between immune biomarkers and clinical symptom improvement. Additional safety blood samples may be required in the event of abnormal values or analysis failure. The blood samples collected for safety laboratory analysis will be destroyed after the analyses have been completed.

The specific parameters being assessed are presented in Table S3 in Multimedia Appendix 1, whereas collection time points can be found in Table S1 in Multimedia Appendix 1.

#### Safety Assessments

The primary safety analysis for this study will include the total number of treatment-emergent adverse events (TEAEs) while also categorizing TEAEs by causality, severity, and seriousness assessments made by the investigator by comparing study drug exposure to placebo.

Trends in safety will also be evaluated for the following assessments: physical examinations, vital signs, laboratory results (hematology, lipid levels, and serum chemistry), pregnancy tests, and discontinuations because of adverse events (AEs).

### Demographic Data and Medical History

At the screening visit, a complete medical history will be compiled for each participant. This history will include the use of antidepressant therapies, GI-related disorders and surgeries, depressive episodes, medical history, baseline signs, and symptoms.

#### Vital Signs

Vital signs, including temperature, blood pressure (systolic and diastolic), pulse, and body weight (using a calibrated weight scale), will be measured at screening, baseline, week 4, and week 8. Blood pressure will be measured with a cuff size appropriate to the participant after the participant has been sitting for 5 minutes.

#### Physical Examination

A complete physical examination will be conducted at the baseline visit. The physical examination will include general appearance, skin, head, ears, eyes, nose, throat, lungs, cardiovascular, abdomen, musculoskeletal and extremities, lymph nodes, and neurological. Other body and organ systems may be examined if clinically relevant.

#### Pregnancy Test

A pregnancy test will be performed at baseline. If pregnancy is discovered in a female participant enrolled in the study before the end of dosing, the study drug will be permanently discontinued, and an end-of-treatment visit will be scheduled. If the pregnancy is discovered in a female participant enrolled in the study after the end of dosing, the participant will continue in the study per protocol. If pregnancy occurs in a male participant’s partner at any time during the study, the pregnancy is to also be reported and followed.

### Adverse Events

#### Overview

An AE is any untoward medical occurrence in a participant administered an investigational treatment, which does not necessarily have a causal relationship with this treatment. An AE can therefore be any unfavorable and unintended sign or symptom temporally associated with the use of the investigational treatment, regardless of whether it is related to the treatment. Each participant will be carefully monitored for the development of AEs during the safety reporting period. Both the frequency and severity of AEs will be collected at the time of consent throughout the study until the 2-week follow-up. AEs will be assessed and recorded at all in-hospital visits or through the phone using questionnaires and probing via discussion; these AEs will be categorized by frequency, severity, and causality [7]. Any clinically relevant abnormalities will be noted by the investigator during the follow-up interviews. All AEs will be recorded in an AE log for each participant. Any instances that lead to serious AEs (SAEs) and any untoward medical occurrences at any dose will be reported to the research ethics board (REB).

A TEAE is an AE that begins during the treatment or worsens a pre-existing medical condition (eg, worsening diarrhea). The treatment period is the period during which a participant receives the investigational treatment.

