### Microbial Ecosystem Therapeutics

Microbial Ecosystem Therapeutic (MET)-2 is an oral, daily administered, novel treatment approach designed to repopulate the gut with microbiota from a healthy donor. MET-2 is a defined microbial community comprised 40 strains of lyophilized bacteria that are lab-grown and purified from a healthy 25-year-old donor’s stool. MET-2 was originally developed by researchers at Queen’s University and the University of Guelph to treat symptoms of early depression and help restore the normal gut flora. The original mixture contained pure cultures of intestinal bacteria, referred to as *Repoopulate* or MET-1, which was composed of 33 strains of bacteria that were chosen for their favorable safety profile [26]. This mixture was then refined, modified, and improved to 40 strains to create MET-2. Capsules were chosen instead of traditional FMT not only to increase acceptability to participants but also to allow for easier administration of the product for consecutive days rather than the use of raw fecal material administered via rectal suspension.

This study aims to evaluate the effects of MET-2 on symptoms of depression using pre- and posttreatment scores for overall depression and specific depressive symptoms. Our primary aim is to demonstrate the efficacy of MET-2 treatment, in comparison with placebo, on mood and related symptoms in participants with depression, using the Montgomery-Asberg Depression Rating Scale (MADRS) [27]. Those with at least a 50% reduction in MADRS scores will be considered successful responders to treatment. The secondary aims are to assess changes in anxiety symptoms, immune marker levels in response to MET-2 treatment, and the safety and tolerability of MET-2 treatment, and to evaluate any potential correlations between early life stress (eg, childhood emotional, physical, or sexual abuse history) and response to MET-2 treatment.

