#### Serious Adverse Events

An SAE is a life-threatening adverse medical event that results in death, requires inpatient hospitalization or prolongation of existing hospitalization, results in persistent or significant disability or incapacity, and results in a congenital anomaly or congenital disability [7]. The study site will document all SAEs that occur (whether related to the study drug) and report them to the sponsor within 24 hours of the site’s first knowledge of the event. The collection period for all SAEs will begin after informed consent is obtained and will end after the procedures for the final study visit have been completed.

All SAEs will be followed until resolution. SAEs that remain ongoing past the participant’s last protocol-specified follow-up visit will be evaluated by the principal investigator and NuBiyota LLC. If both parties agree that the participant’s condition is unlikely to resolve, the principal investigator will determine the follow-up requirement.

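### The window for new-onset treatment-emergent adverse events closes at the last dose, so the primary safety analysis leaves out new events from the two follow-up weeks in which adverse events are still collected

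*Protocol article*

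**What the plan says.** Safety Assessments sets the content of the main safety comparison: "The primary safety analysis for this study will include the total number of treatment-emergent adverse events (TEAEs"), classified further by causality, severity and seriousness and compared between active and placebo. Trends in examinations, vital signs, laboratory values, pregnancy tests and discontinuations for adverse events are looked at beside it.

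Adverse Events (Overview) gives the definition: "A TEAE is an AE that begins during the treatment or worsens a pre-existing medical condition", with diarrhea that gets worse as the example. The next sentence closes the window: "The treatment period is the period during which a participant receives the investigational treatment".

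Collection runs longer than that. The same section states: "Both the frequency and severity of AEs will be collected at the time of consent throughout the study until the 2-week follow-up". For serious events, the section Serious Adverse Events states: "The collection period for all SAEs will begin after informed consent is obtained and will end after the procedures for the final study visit" are complete.

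Dosing lasts 6 weeks (Administration of Study Drug), and the last visit comes 2 weeks later (Setting). The product is described as "designed to repopulate the gut with microbiota from a healthy donor" (Microbial Ecosystem Therapeutics). Engraftment in stool is a secondary endpoint, and several depression and anxiety scales and the immune markers are assessed to week 8 (Secondary Endpoints).

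**The concern.** The article uses two windows, and the shorter one governs the main safety comparison. An adverse event that first appears after the last capsule is recorded on the log but does not meet the definition of a TEAE, so it does not enter the comparison with placebo that Safety Assessments calls primary. This also applies to a new serious event.

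The cut-off fits this trial poorly. The product is intended to establish bacteria in the gut, and the trial measures whether it does. The Discussion (Optimal Treatment Methods) raises the possibility of a lasting effect on mood after treatment, and efficacy is followed to week 8. Possible benefit after dosing is therefore assessed, while new-onset harm in the same two weeks is left out of the headline safety result. Because the article itself sets this definition, an analysis plan that follows it would carry the gap forward.

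**Working it through.** The plan states no figure that depends on this window, so there is none to reproduce. The check sets the two windows side by side and then sizes the gap.

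**Inputs**
- Dosing: 6 weeks = 42 days (Administration of Study Drug).
- Follow-up after dosing: 2 weeks = 14 days (Setting).
- Arm size: 30 (Study Design).
- Adverse event rates: none given, so the rate ratio *r* and the probability *p* below are assumptions.

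**Step 1. Which events count, as written, for a completer**

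| Event | Logged? | TEAE? |
|---|---|---|
| New onset while on treatment (42 days) | Yes | Yes |
| New onset in the 14 days after dosing | Yes | No |
| New serious event in the 14 days after dosing | Yes | No |
| Worsening of a pre-existing condition in those 14 days | Yes | Yes, read literally |

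The last row follows because the worsening limb of the definition carries no time window. New diarrhea in week 7 is not a TEAE, while diarrhea present before the trial that worsens in week 7 is.

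**Step 2. Share of time**

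14 / (42 + 14) = 14/56 = 25% of the days after first dose lie inside collection but outside the window for new-onset TEAEs.

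**Step 3. Share of new-onset events**

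Let *r* be the follow-up event rate divided by the on-treatment rate. The share left out is 14*r* / (42 + 14*r*):
- *r* = 0.25: 3.5/45.5 = 7.7%
- *r* = 0.5: 7/49 = 14.3%
- *r* = 1.0: 14/56 = 25.0%
- *r* = 1.5: 21/63 = 33.3%

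**Step 4. Participants affected per arm**

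Let *p* be the chance that a participant has a new-onset event during follow-up. In an arm of 30, the expected number with an excluded event is 30*p*, and the chance of at least one is 1 − (1 − *p*)^30:
- *p* = 2%: 0.6 expected, 45.5% chance of at least one
- *p* = 5%: 1.5 expected, 78.5%
- *p* = 10%: 3.0 expected, 95.8%

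**Step 5. Dating of onset**

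The Vital Signs section lists measurements at weeks 4 and 8 but none at week 6. An abnormality first seen at week 8 cannot be placed before or after the last dose from those measurements alone, so under the present definition its status would be unclear.

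**The case against.** The strongest reply is that little is lost. All adverse events to the 2-week follow-up go into a log and are categorized by frequency, severity and causality. Serious events are collected to the final visit, and the expedited reporting rules make no reference to the TEAE window. Vital-sign trends include week 8. An intolerance that makes someone stop has begun on treatment and so is a TEAE, and discontinuations for adverse events are examined separately. All loading and booster doses fall within days 1 to 30, so an equal event rate in follow-up is not obvious. All of this stands. It limits the point to what the primary safety comparison contains, but it does not reconcile the two windows.

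A reader might infer more than the article supports:
- **That post-dosing events vanish.** They do not. They are recorded and left out of one summary, and worsening events may still count.
- **That the analysis wrongly counts events instead of participants.** Safety Assessments says the analysis will include the event total. It fixes no test on that total and does not rule out participant counts. Such tables are commonly left to the analysis plan, which the Statistical Analysis section announces, so their absence is no error here.
- **That someone stopping at week 2 has 6 of 8 weeks (75%) excluded.** This assumes observation to week 8 after early stopping, which the article does not state in general.
- **That the loss falls mainly on the arm with more discontinuations.** No discontinuation rates are given.
- **That exposure continues after the last capsule.** Repopulation is the design intent and engraftment is an endpoint to be measured. Persistence after dosing is plausible but not stated.

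**Conclusion.** The point holds for new-onset events. The article ends the TEAE window with dosing, collects adverse events for two more weeks, and rests its primary safety analysis on TEAEs. The 25% is a share of time, exact for a participant who takes the full 6 weeks of treatment and attends follow-up at week 8. The 7.7% to 33.3% range for events rests wholly on the assumed rate ratio of 0.25 to 1.5, and the per-arm figures rest on the assumed 2% to 10% risk. Neither is an estimate from the trial. The direction of any effect on the comparison between arms cannot be told from the document. This should be corrected, but it does not threaten the trial: the events are logged and the definition can still be aligned before the analysis plan is finalized.

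**What to change.** In Adverse Events (Overview), define a TEAE as an adverse event that starts or worsens from the first dose through the 2-week follow-up visit, or through the last safety contact for a participant who stops early. Apply the same window to both limbs of the definition, and have Safety Assessments refer to it. Show events with onset during dosing and after dosing separately, so that the on-treatment picture remains visible, and state how an event that cannot be dated is classified.

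The cost is a change of wording and one extra table, and reported counts may rise slightly. For participants followed to week 8 no new data are needed, because collection already runs that far.

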#### Serious Adverse Events

An SAE is a life-threatening adverse medical event that results in death, requires inpatient hospitalization or prolongation of existing hospitalization, results in persistent or significant disability or incapacity, and results in a congenital anomaly or congenital disability [7]. The study site will document all SAEs that occur (whether related to the study drug) and report them to the sponsor within 24 hours of the site’s first knowledge of the event. The collection period for all SAEs will begin after informed consent is obtained and will end after the procedures for the final study visit have been completed.

All SAEs will be followed until resolution. SAEs that remain ongoing past the participant’s last protocol-specified follow-up visit will be evaluated by the principal investigator and NuBiyota LLC. If both parties agree that the participant’s condition is unlikely to resolve, the principal investigator will determine the follow-up requirement.

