#### Reporting of Expedited Safety Reports

A suspected unexpected serious adverse reaction (SUSAR) is an SAE that occurs in a participant, the nature or severity of which is not expected per the applicable product information (ie, the investigator’s brochure).

The sponsor and investigator will report any SUSARs concerning the drug that has occurred in the study to regulatory authorities:

If it is neither fatal nor life-threatening, within 15 days after becoming aware of the information.If it is fatal or life-threatening, within 7 days after becoming aware of the information. The sponsor and investigator shall, within 8 days after having informed the REB and Health Canada of a fatal or life-threatening SUSAR, submit a complete follow-up report in respect of that information that includes an assessment of the importance and implication of any findings made.

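### The SAE definition is wrongly worded: it makes life-threatening a condition of every SAE, joins the outcomes with *and*, and so contradicts the protocol's own 15-day SUSAR rule

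*Protocol article*

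**What the plan says.** The only definition of an SAE in the article is in the section Serious Adverse Events. It opens "An SAE is a life-threatening adverse medical event that results in death, requires inpatient hospitalization or prolongation of existing hospitalization" and continues "results in persistent or significant disability or incapacity, and results in a congenital anomaly or congenital disability".

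Three other rules use the term:

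- **Report to the sponsor** (same section). Sites document all SAEs and "report them to the sponsor within 24 hours".
- **Follow-up** (same section). "All SAEs will be followed until resolution", with a further provision for those still ongoing after the last scheduled visit.
- **Expedited reporting** (Reporting of Expedited Safety Reports). "A suspected unexpected serious adverse reaction (SUSAR) is an SAE that occurs in a participant", with the added condition that it is unexpected. Two deadlines follow. One is 7 days for fatal or life-threatening cases. The other reads: "If it is neither fatal nor life-threatening, within 15 days after becoming aware of the information".

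The primary safety analysis (Safety Assessments) counts treatment-emergent adverse events and compares study drug with placebo, "categorizing TEAEs by causality, severity, and seriousness assessments made by the investigator".

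**The concern.** The sentence has two faults. First, life-threatening is attached to the event itself, so every SAE must satisfy it before any outcome is considered. Second, the outcomes are connected by *and*; the word *or* appears only inside single criteria.

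The term decides which events go to the sponsor within 24 hours, which can become SUSARs, and which are tabulated as serious. Three sites in two countries have to apply it alike. The population has major depression, so an inpatient admission that nobody judges life-threatening is an event one can foresee. Followed as worded, the definition would leave such an admission out of all three.

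**Working it through.** The check is logical; no figure in the protocol bears on it. Write L for life-threatening, D for death, H for hospitalization or its prolongation, I for disability or incapacity, and C for a congenital anomaly or disability. The sentence can be read in three ways:

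1. **Literal:** SAE = L and D and H and I and C.
2. **Lenient on *and*:** SAE = L and (D or H or I or C).
3. **Alternatives:** SAE = L or D or H or I or C.

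Each reading is then set against the rules that depend on it.

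**The 15-day class.** A SUSAR is an SAE, so this class is SAE and not-D and not-L.
- Reading 1 requires both L and D: empty.
- Reading 2 requires L: empty. Every SUSAR would fall in the 7-day class, and the two-tier deadline would have no purpose.
- Reading 3 leaves (H or I or C) and not-D and not-L: not empty.

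**Follow-up to resolution, with provision for ongoing SAEs.**
- Reading 1: every SAE includes death, so the rule makes no sense.
- Readings 2 and 3: the rule can be applied to non-fatal SAEs. This conflict therefore arises from the *and*, while the 15-day conflict arises from the position of life-threatening as well.

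**Example events under each reading.**

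| Event | Reading 1 | Reading 2 | Reading 3 |
|---|---|---|---|
| Inpatient admission, not life-threatening | no | no | SAE |
| Lasting disability, not life-threatening | no | no | SAE |
| Life-threatening, with none of the listed outcomes | no | no | SAE |
| Life-threatening, with admission | no | SAE | SAE |

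Only reading 3 fits both the 15-day deadline and the follow-up rule, and it is the one reading that the sentence does not express. The first two rows are the loss that remains after the generous treatment of *and*. Such events would carry no 24-hour report, could not be SUSARs, and would be non-serious in the comparison of adverse events between arms.

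**The case against.** The strongest reply is that the surrounding text already rules out the literal reading. A deadline for SUSARs that are neither fatal nor life-threatening presupposes SAEs of that kind, and following SAEs until they resolve presupposes survivors. A reader might infer from the definition alone that practically no SAE could ever be recorded in this trial. The document does not support that: no site could apply the literal sentence together with the rules that follow it. It would be equally wrong to infer that the sponsor chose a narrow definition. This looks like a drafting slip.

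Other points also soften the effect:

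- The article condenses a full protocol that is not shown, and the sentence carries a literature citation. The wording used at the sites may be correct.
- Study Conduct commits the sites to ICH GCP and applicable regulations, and the sponsor to seeing that they have the necessary operating procedures. Study Monitoring requires SAE documentation to be verified.
- The Adverse Events overview has every adverse event logged and sends untoward occurrences in general to the research ethics board. An admission would not vanish from the record.
- Seriousness is assessed by the investigator, who may well apply the usual understanding.

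All of this lowers the practical risk. None of it corrects the sentence. Study Conduct requires compliance with the protocol as well as with GCP and does not restate the criteria, so a site would have to override explicit wording to classify correctly. The ethics board is a different recipient, no 24-hour limit is stated for that route, and it settles neither SUSAR status nor the serious category. Nor is this detail left to a fuller document: the article gives a complete definition and misstates it.

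**Conclusion.** Wrong as written. The SAE definition contradicts the 15-day SUSAR rule on both readings that its wording allows, and contradicts the follow-up rule on the literal one. Taken at its most lenient, it still excludes admissions and lasting disabilities that are not life-threatening from the 24-hour report, SUSAR reporting and the serious category of the safety analysis.

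The size cannot be given as a number, because the document offers no basis for how many events would be affected. Whether any event would in fact be misclassified depends on the full protocol, CRF and site procedures, which are not shown. The conclusion concerns safety reporting only; the primary endpoint, the efficacy analysis, alpha and the sample size do not change. It rests on the article's text alone and assumes no outside definition.

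**What to change.** Reconcile the two sections by turning the criteria already listed into alternatives, with life-threatening as one of them. For example: an SAE is any adverse event that meets at least one of the following: (a) death; (b) a threat to life; (c) inpatient admission, or a longer stay for someone already in hospital; (d) disability or incapacity that is lasting or significant; (e) a congenital anomaly or disability. Each item can keep its present phrasing; what changes is that any one of them suffices.

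Then confirm that the full protocol, the CRF and its guidance, and the specification of the safety tables carry the same sentence, so that all three sites classify seriousness alike.

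The cost is one sentence and a consistency check, with an amendment only if the full protocol carries the same error. Visits, sample size and treatment are unaffected. The SAE count may be higher than under the present wording.
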